### Analyses

The economic evaluation will be comprised of both a cost-effectiveness analysis (CEA) and cost-utility analysis (CUA) and will be performed from a societal perspective. All available data on costs and outcomes will be analysed according to the intention-to-treat principle. Data gathered with the cost interview will first be checked for adherence to questionnaire routing, illogical answers, unrealistic cost estimates and outliers. For any problems in the data that cannot be solved through logic, decision rules will be established. A decision rule could apply a specific limit to volumes of costs, e.g. the maximal hours patients spend per day on caring for their children can be limited to eight for patients who report doing this for 24 hours per day. For intermittent missing values at the item level of the cost interview the mean values of previous and subsequent assessments will be imputed to allow calculation of total costs. Missing values on total scores or other outcomes will not be imputed. Unrealistic or extreme values will be investigated per case and corrected when appropriate. Volumes of resource use as measured by the cost interview will be multiplied by their corresponding unit costs and then summed to provide an overall total cost. Unit costs will be based on standard unit prices for each country (e.g. in the Netherlands: Hakkaart-van Roijen et al. [59] for cost prices of healthcare services [59]) when available and on (averaged) tariffs otherwise. Cost prices will be expressed in Euros for the same base year and indexed using consumer price indices when required. Cost prices expressed in currencies other than Euros will be converted using purchasing power parities. In addition, to account for the three year time horizon of this RCT, cost prices will be discounted according to the guidelines. When neither standard unit prices nor tariffs are available for specific resource items in specific countries, alternative strategies for the valuation of resource use will be considered. When for a subset of resource items the unit costs are known in all countries and for all other resource items there is a unit cost available in at least one country, the unit cost of a resource item that is not available in one or more countries can be estimated through a procedure called market-basket based imputation [60]. In base-case analysis, country-specific unit costs will be used to value resource use for each country. Sensitivity of the results to differences in unit prices between countries will be analysed by valuing resource use in all countries using unit prices of a single country. Productivity losses will be valued by the human capital approach through multiplication of the total number of hours lost with the national average hour wage. Shadow prices will be used to value informal care and lost productivity in study and voluntary work. The primary clinical outcome for the CEA will be the BPD Severity Index (BPDSI) score and for the CUA primary utility scores will be derived from the EuroQol-5D. Cost-effectiveness and cost-utility data will be analysed with multilevel modelling techniques. The net monetary benefit will be used to express cost-effectiveness, and results will be expressed in cost-effectiveness acceptability curves. Net monetary benefit (NMB) will be calculated for a range of values for the amount decision makers are willing to pay (WTP) for an additional unit of effect, following: NMB = ∆E*WTP- ∆C, where ∆E is the difference in effects and ∆C is the difference in costs [61]. To accommodate the skewness that is typically observed in cost data, costs (or NMB) can be assumed to follow a gamma or log-normal distribution. Baseline covariates will be used to adjust for potential differences at baseline and to reduce standard errors. Results will be expressed in cost-effectiveness acceptability curves that display the probability, based on the available evidence, that GST can be considered cost-effective for a range of WTP values. For these types of analyses, a Bayesian approach is the most natural, since it allows direct and intuitive statements to be made regarding the probability that a treatment is cost-effective, based on the available evidence [62]. Furthermore, Bayesian methods allow flexible joint modelling of costs and effects, thereby facilitating sensitivity analyses regarding different methodological approaches for specification and parameterization of the model. Sensitivity analyses will be performed to address uncertainty regarding methodology, model specification and prior distributions.

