At baseline, the Interview for Traumatic Events in Childhood (ITEC) will be conducted. This is a retrospective, semi-structured interview for childhood maltreatment including sexual, physical and emotional abuse and physical and emotional neglect [28]. At follow-up, patients are assessed for recovery from BPD as well as the most common comorbidities by trained interviewers using the following sections of SCID-I for DSM-IV-Tr: affective disorders (including bipolar disorder I and II), anxiety disorders, eating disorders and substance disorders; and the following sections of SCID-II for DSM-IV-Tr: avoidant, dependent, obsessive-compulsive, paranoid, schizotypal, schizoid, histrionic, narcissistic, antisocial and borderline PD. Since only current diagnoses need to be considered for the assessment of recovery from BPD and comorbidity, the recall period for these shortened SCIDs is limited to six months. Only when a patient will otherwise become a study dropout (e.g. due to unwillingness to come to the centre for assessments), they can fill in questionnaires at home. Interviews are then conducted by telephone. By doing so, the occurrence of missing data will be reduced.

Due to the nature of the study, blinding of participants is not possible. Except for the cost interview, which contains specific questions on which treatments patients have received, assessments will be performed by blinded local research assistants. The cost-interview, containing questions on health care utilization that would unblind the condition will be done by a nonblinded research assistant. This assistant will also monitor treatments provided in TAU. Furthermore, this nonblinded research assistant will collect treatment session recordings that are needed for supervision and validation of treatment adherence. After checking the quality of the recording, the sample of recordings that is needed will be stored.

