Another degree of complexity is added to economic evaluations in the field of mental health, as opposed to somatic disorders, due to the fact that once costs and consequences are measured, their interpretation can be difficult. No consensus exists on the extent to which particular costs need to be included or not and how they need to be valued [73]. For example, although informal care provided by family and friends is very relevant to patients with BPD, it can be difficult to know which amount of care is specifically due to mental health problems and which amount they would have received anyway. Similarly, productivity losses can be the result of being under treatment, yet patients with mental health problems are also less likely to be employed or could have already lost their job before having their diagnosis [74]. Furthermore, although the volumes of production losses in paid work, voluntary work, study, and household activities as well as contacts with the GP and medication use are explicitly measured separately for being BPD-related or not, this division cannot always be reliably made. For example, a leg injury by itself may seem unrelated to BPD at first sight, but less so when it is the result of a suicide attempt. In such cases, the analyst is guided by the information provided, while at the same time being aware that this information may or may not be complete. In cases where there is sufficient information to attribute a somatic complaint to an underlying mental health complaint, patient answers are overruled. Reliability can also be an issue when rather high out-of-pocket expenses are reported [72].

In addition to the evaluation of clinical effectiveness and the economic evaluation, a series of additional investigations will be performed in this RCT that consist of an assessment of the integrity of GST, in terms of adherence to the GST protocol, an investigation into the opinions of major stakeholders and analyses of variables that might mediate treatment response. The qualitative data on the experiences of patients and therapists are considered as complementary to the quantitative methods that will be employed in this study. By interviewing patients and therapists, potentially important, yet unanticipated, issues may be detected. Furthermore, this type of data collection can give valuable insight into the contextual factors that play a role in the effectiveness of GST and its implementation.

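### Extreme cost values are corrected case by case on interviews that show the treatment received, with no masking stated for the person correcting them

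*Protocol article*

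**What the plan says.** Four parts of the protocol article bear on this point.

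- **Economic evaluation, Analyses (general rule).** Cost-interview data are first checked for routing errors, illogical answers, unrealistic estimates and outliers. Then: "For any problems in the data that cannot be solved through logic, decision rules will be established". The one example, with the limits in daily hours, is a cap: "the maximal hours patients spend per day on caring for their children can be limited to eight for patients who report doing this for 24".
- **Economic evaluation, Analyses (extreme values).** A separate sentence follows: "Unrealistic or extreme values will be investigated per case and corrected when appropriate". No threshold, criterion or responsible role is given.
- **Assessments (text after Table 1).** The exception to blinded assessment is "the cost interview, which contains specific questions on which treatments patients have received". The article continues: "The cost-interview, containing questions on health care utilization that would unblind the condition will be done by a nonblinded research assistant". The Discussion repeats that blinding is impossible for this interview.
- **Discussion, on attributing costs to BPD.** The article accepts that the split between BPD-related and unrelated volumes is not always reliable. It leaves doubtful cases to the analyst, who works from whatever the record contains and knows that it could be partial. It adds: "In cases where there is sufficient information to attribute a somatic complaint to an underlying mental health complaint, patient answers are overruled".

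Cost-effectiveness belongs to the main objective (Background). The cost difference enters net monetary benefit directly.

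**The concern.** An unblinded cost interview is unavoidable, and the article says so openly. Editing the answers afterwards is a separate step, and that step could be masked. As written, the decision that a large value is unrealistic, and what should replace it, is a judgement made one record at a time from an interview that reveals treatment.

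The article expects skewed costs, and its Discussion expects some doubtful high out-of-pocket amounts. Values open to correction will therefore occur, and in skewed data they carry much of the arm mean. If the judgement is applied more strictly in one arm, the cost difference moves, in either direction. Intention-to-treat analysis does not protect against this, because every patient stays in the assigned arm while the recorded outcome changes. A gamma or log-normal model for costs does not protect either, because it is fitted to the values after editing.

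**Working it through.** The article states no figure to reproduce, so the check is mainly a comparison of its sections.

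1. **Is the discretion stated, or only left unsaid?** It is stated. The extreme-value sentence provides for per-case correction where judged appropriate. It stands beside the promise of decision rules and is not made subject to them.
2. **Does the record reveal treatment?** Yes. The Assessments section says the health-care questions would unblind. The Treatment as usual section also bars schema therapy from the control arm, so a record showing schema therapy points to the assigned arm.
3. **Is the correcting step masked?** Blinding is described in Assessments and in the Discussion for interviewers and assessors only. Nothing is said either way about the person who cleans or recodes cost data.
4. **Do corrected values reach the result?** Yes. Volumes are multiplied by unit costs and summed to a total cost. Net monetary benefit is NMB = ∆E × WTP − ∆C, so a shift of x in ∆C changes NMB by −x at every willingness-to-pay value.
5. **Would a planned sensitivity analysis show the effect?** Those named cover single-country unit prices, EQ-5D tariffs, methodology in general, model specification and priors. None is named that uses uncorrected costs.
6. **Does the re-attribution of complaints reach the same result?** Not on the text. The total is summed over all volumes and is not restricted to BPD-related items. Moving an item from unrelated to BPD-related may leave the total unchanged.

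**Leverage under assumptions.** This shows only how sensitive an arm mean can be. It does not estimate bias in this trial.

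- Arm size: 448 / 2 = 224.
- Assumed: one log-normal cost total per patient with mean 1 and a coefficient of variation (CV) of 1 to 2. The article gives no cost SD.
- Extreme case: the largest k values are lowered to the next-largest value in one arm only (4,000 simulated arms per setting).
- SE of the difference, ignoring centre effects: CV × √(2/224).

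| CV | SE of difference | Shift, k = 1 | Shift, k = 5 | Shift, k = 11 |
|---|---|---|---|---|
| 1 | 0.0945 | 0.0091 (0.10 SE) | 0.0353 (0.37 SE) | 0.0678 (0.72 SE) |
| 1.5 | 0.1417 | 0.0191 (0.13 SE) | 0.0663 (0.47 SE) | 0.1191 (0.84 SE) |
| 2 | 0.1890 | 0.0309 (0.16 SE) | 0.1007 (0.53 SE) | 0.1702 (0.90 SE) |

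Shifts are fractions of mean cost. One wholly one-sided correction has little effect; five or more could matter. Corrections falling evenly across arms would largely cancel in the difference.

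**The case against.** The strongest reply is that this is a journal article. Who cleans the data, whether that person is masked and which thresholds apply may stand in a fuller protocol or data-handling plan. That is fair for the masking and the thresholds, and their absence alone would be no finding. It does not dispose of the extreme-value sentence, which states a discretionary method.

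The article also promises decision rules and sensitivity analyses on methodology. Both are partial safeguards. The rules are not yet fixed, however, and the sensitivity analyses do not name the cleaning step.

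Three stronger readings are tempting, and the documents support none of them.

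- **That whoever corrects a value knows the arm.** The article unblinds the interviewer and shows that the interview reveals treatment. It does not say which items the corrector sees.
- **That overruling patients' answers shifts the cost endpoint.** That step concerns the BPD-related split, and the stated total does not depend on the split.
- **That the child-care cap gives the size of the bias in money.** The cap is the article's example of a decision rule, which would apply to any patient with that report in either arm. The article assigns no price to a patient's own child-care hours. A money figure would also require an assumption about how corrections fall between arms.

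**Conclusion.** The point holds as a design weakness in the economic evaluation. A stated, criterion-free, per-case correction is applied to records that reveal treatment, and no masking is stated for the person making it. It could bias the cost difference and the acceptability curves in either direction.

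The documents show the opportunity for bias and not its occurrence. They do not allow its size to be calculated, and the simulated shifts rest on an assumed CV and on corrections confined to one arm. The BPDSI-IV analysis is not touched. The change is worth making because cost-effectiveness is half of the main objective and the remedy is cheap.

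**What to change.** In Economic evaluation, Analyses, replace the per-case sentence with a procedure:

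1. Set the outlier and capping rules on data pooled over arms, and apply them identically to both arms.
2. Work on a file with the arm code removed and, where feasible, the mental-health-treatment items split off. Check those items with the same pre-set rules.
3. Log every correction, with the old value, the new value and the reason. Lock the cleaned file before the arm is merged.
4. Add a sensitivity analysis repeating the base case on uncorrected cost data.

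If BPD-related costs are to be analysed separately, apply the same masking to the re-attribution described in the Discussion, and keep the free text that attribution needs. If they are not, that step needs no change for this purpose.

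The cost is some data-management work to split the interview export and one extra analysis run. No new data are required. The downside is that a few corrections needing treatment context could be made only by the pre-set rules.

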### Utility measures

#### EuroQol-5D-3 L (EQ-5D-3 L)

The EQ-5D-3 L is a generic, self-assessment instrument used for measuring health-related quality of life at the time of assessment [56]. It consists of five questions, each related to a specific dimension of health status: mobility, self-care, usual activity, pain/discomfort and anxiety/depression. The EQ-5D has been translated in the languages of all participating sites [57]. The descriptive profiles, generated by the EQ-5D-3 L are valued using social tariffs for the EuroQol to generate utilities, which reflect a population’s preference for a particular health profile.

In base-case analysis, country-specific tariffs will be used for valuation when available. For the Netherlands, Germany and the UK national tariffs are available, whereas for Greece and Australia they are not [57]. For these countries, proxy tariffs will be used as an alternative (e.g. tariffs for Europe and New-Zealand, respectively). Sensitivity analyses will be performed that make use of country-specific tariffs for the valuation of health profiles of all patients.

Utilities will be used to calculate Quality Adjusted Life Years (QALYs) by multiplying change in utility between assessments by the duration of the time period between assessments. Through the use of statistical regression, potential baseline differences in QALYs can be adjusted for [58].

In addition, the EuroQol thermometer will be scored in a range between 0 and 100 to provide a single index measure for a patient’s health status [56].

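### The economic analysis allows net monetary benefit, which can be negative, to follow a gamma or log-normal distribution; that choice is sound only for costs

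*Protocol article*

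**What the plan says.** The relevant text is in the protocol article, Economic evaluation, Analyses.

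- NMB is the measure of cost-effectiveness: "NMB = ∆E*WTP- ∆C, where ∆E is the difference in effects and ∆C is the difference in costs".
- It is evaluated across WTP values: "Net monetary benefit (NMB) will be calculated for a range of values for the amount decision makers are willing to pay". The end points of the range are not given. The results are to be shown as acceptability curves.
- The distributional choice is introduced with a reason, "To accommodate the skewness that is typically observed in cost data", and then stated: "costs (or NMB) can be assumed to follow a gamma or log-normal distribution".
- Costs per patient are resource volumes "multiplied by their corresponding unit costs and then summed to provide an overall total cost".

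Under Utility measures, the EQ-5D section builds QALYs by "multiplying change in utility between assessments by the duration of the time period between assessments".

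The Analyses section also plans multilevel modelling, notes that a Bayesian approach makes it possible to model costs and effects together, and announces sensitivity analyses on model specification. It mentions no sign change, shift or other transformation of NMB.

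**The concern.** The reason given for the gamma or log-normal is the skewness of costs. It does not carry over to NMB. Costs are non-negative and typically have a long right tail. NMB subtracts them, so it can fall below zero and its long tail points left. The permitted families are therefore wrong for NMB in support and, where costs dominate, in direction of skew.

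The comparison of cost-effectiveness is part of the main study objective, and the acceptability curve is how it will be reported. An analyst who used the NMB option would meet a model that cannot be fitted at the low end of the curve. The ways round that, such as a shift, are not in the plan and would be chosen after the data are in.

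**Working it through.** The plan states no figure to reproduce. The check compares the support of the distributions with the values NMB can take.

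**Inputs from the article.** The NMB formula, a range of WTP values, costs as sums of volumes times unit costs (so not below 0), and QALYs built from changes in utility (so possibly negative). The printed formula is incremental. A regression on patient data needs the patient-level form, NMB_i = E_i × WTP − C_i, which is an inference from the planned multilevel model. Both readings are checked.

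**Patient-level reading.**

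1. At WTP = 0, NMB_i = −C_i ≤ 0 for everyone. It is negative for every patient with any cost, and exactly 0 for a patient with none.
2. Gamma and log-normal densities are zero at negative values. For example, with a gamma of shape 2 and scale 10,000, and a log-normal with log-SD 1 and median 10,000, the log-density at −5,000 is minus infinity for both. At +5,000 it is −10.40 and −9.68. One negative observation makes the whole likelihood zero.
3. For WTP > 0 and E_i > 0, NMB_i is positive only if WTP > C_i / E_i. With an assumed cost of EUR 30,000 and 1.8 QALYs, that is 30,000 / 1.8 = EUR 16,667. With an assumed QALY change of 0.3, it is 30,000 / 0.3 = EUR 100,000. If E_i ≤ 0, NMB_i is not positive at any WTP.

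**Incremental reading.** The acceptability curve plots P(incremental NMB > 0). Any distribution confined to positive values gives P = 1 at every WTP, whatever the data. At WTP = 0 the quantity is −∆C, so the curve should there show the probability that GST costs less than TAU.

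**Illustration only.** All inputs here are assumed: 448 simulated patients; gamma costs with mean EUR 10,000, 30,000 or 60,000 and coefficient of variation 0.7 or 1.2; three-year QALYs normal with mean 1.8 and SD 0.6, limited to −0.9 to 3; QALYs as utility change normal with mean 0.3 and SD 0.5. Share of patients with NMB ≤ 0, lowest to highest of the six cost scenarios:

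| WTP per QALY (EUR) | Total QALYs | QALYs as utility change |
|---|---|---|
| 0 | 100% | 100% |
| 1,000 | 71-100% | 90-100% |
| 20,000 | 4-64% | 56-97% |
| 80,000 | 0.4-14% | 37-74% |

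**Skewness.** Simulated costs had skewness of about +1.5 to +2.4, so NMB at WTP = 0 had −1.5 to −2.4. As WTP rises, the effect term dominates and the skew fades. With the symmetric effects assumed here it reached at most +0.18. Strong left skew is thus a feature of low and moderate WTP.

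**Possible rescues.** Modelling −NMB works only where every NMB is negative, so it fails once signs are mixed. A shift needs an arbitrary constant, possibly a different one at each WTP.

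**The case against.** The wording is permissive, and the faulty part is a two-word parenthesis. The same sentence offers the valid choice of a gamma or log-normal on costs. The section also opens the route to joint modelling and promises sensitivity analyses. The fault is largely self-revealing, because an unshifted model on negative values will not run. The primary clinical analysis and the sample size are untouched. All of this stands, and it limits the severity. It does not make the option valid. Nor is this detail left to a fuller document, since the article affirmatively names a distribution that does not fit.

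A reader might infer more than the article supports:

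- **That NMB is negative for every patient across the low WTP range.** This is free of assumptions only at WTP = 0 (for patients with any cost). Above that the signs are mixed to a degree the article's inputs cannot settle.
- **That shifting NMB by a constant must change the estimated difference.** The same constant added to every patient leaves the difference in arithmetic means unchanged. Fitted results may change under a log-normal model, a log link with covariates, or through the mean-variance relation, but not necessarily. The article proposes no shift.
- **That the cost-effectiveness analysis rewards deterioration,** because "The primary clinical outcome for the CEA will be the BPD Severity Index (BPDSI) score" and a higher score is worse. The article does not say that a higher raw score counts as benefit. Coding improvement as positive is a detail that a condensed article may leave out.

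**Conclusion.** The concern holds for the NMB option only. A gamma or log-normal is reasonable for costs and wrong as written for NMB, on the patient-level and the incremental reading alike. Two results need no assumed costs or effects: no patient has positive NMB at WTP = 0, and a positive-only distribution on incremental NMB fixes the probability of cost-effectiveness at 1. The shares above WTP = 0 rest on assumed inputs and show only that mixed signs may persist well up the range. Severity is minor to moderate. A reader might conclude that the economic evaluation as a whole cannot be fitted validly, but the article does not support that, because a valid model is already permitted in the same section.

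**What to change.** In Economic evaluation, Analyses:

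1. Delete the words *(or NMB)* so that the gamma or log-normal applies to costs only.
2. State that costs and effects are modelled jointly, with centre random effects, as the planned multilevel and Bayesian approach already allows.
3. State that incremental NMB at each WTP, and the acceptability curve, are derived from the posterior of the arithmetic mean differences in cost and effect.

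Incremental NMB can then take either sign, and the skewness of costs is handled where it arises. The cost is a change of wording and slightly more modelling work. No additional data or patients are needed.
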